## Objectives of the study and expected outcomes

The specific objectives of this project are the following:To test the short- and long-term efficacy of the program in preventing weight regain and promoting weight loss maintenance, promoting new eating behaviors, decreasing psychological distress, enhancing individual self-concept, and addressing other psychological outcomes.To test the utility, feasibility, and perceived satisfaction with APOLO-Bari in terms of compliance with proposed tasks, log-in frequency, and direct evaluation of the satisfaction of participants. Participants with higher log-in frequency and compliance with monthly assessments are expected to report better weight outcomes, higher levels of satisfaction with weight loss and surgical treatment, and lower scores on the self-reported measures, thus reflecting better psychosocial functioning.To study weight regain by exploring the temporal courses of eating-related features and predictors of weight regain. We expect to identify fluctuations in key behaviors that precede weight regain.

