### Subjects

Participants (male and female) between 18 and 65 years of age who underwent bariatric surgery (sleeve gastrectomy and gastric bypass) at least 12 months and not more than 20 months previously will be recruited. This timeframe is used to anticipate the period when patients appear to be at risk of weight regain (12–24 months postoperatively) [2] and when they need help coping with lifestyle adjustments.

For the purpose of this study, patients who initially lost weight successfully after surgery will be included. We seek to exclude potential medical or surgical problems that are not related to lifestyle and psychological adjustment and that could be implicated in and limiting to the initial weight loss. Furthermore, given that our ultimate objective is to prevent weight regain, significant initial weight loss is required. Significant weight loss will be considered when the percentage of excessive weight loss is higher than 30. Furthermore, participants who present with significant weight regain (more than 15 % of the total weight loss) since the nadir weight at the time of registration will be excluded. Other specific exclusion criteria include the following:No regular internet access;Inability to read and understand Portuguese instructions;Lack of willingness to have or create an email account;Presence of an active psychiatric disorder (e.g., bipolar disorder, psychotic disorder, suicidal ideation, eating disorders);Intake of weight-affecting drugs;Concomitant weight loss treatment besides treatment as usual;Pregnancy or lactation.

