#### Anthropometric measures

Participants will be instructed to report their weight based on a standardized assessment self-reported using the same scale on the same day of the week under the same conditions (the time of day and without clothes). The program will ask participants to report their weight once a month in one of their weekly assessments as part of their self-monitoring tasks. Both the intervention group and the control group will have their height and weight measured by the research team at baseline (*T*_b_), at 4- and 8-months midterm assessment (*T*_m4_, *T*_m8_), at the end of the intervention (final; T_*f*_), and at 6- and 12-months follow-up (*T*_fu6_, *T*_fu12_). The weight history of participants (e.g., highest and lowest weight since adulthood, pre-surgery weight, and lowest weight since surgery) will be self-reported.

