### Primary and secondary outcome measures

The primary outcome measure will be weight regain assessed at baseline (*T*_b_), end of treatment (*T*_f_), and follow-up (*T*_fu6_ and *T*_fu12_). Other weight outcome measures, such as variance in weight loss estimations, will be tested. The following formulas will be used to compute these outcomes [40]:

$$ \mathrm{Percentage}\ \mathrm{of}\ \mathrm{total}\ \mathrm{weight}\ \mathrm{regain} = \left(\frac{\mathrm{current}\ \mathrm{weight}-\mathrm{nadir}\ \mathrm{weight}}{\mathrm{weight}\ \mathrm{presurgery} - \mathrm{nadir}\ \mathrm{weight}}\right)\times 100; $$

$$ \mathrm{Percentage}\ \mathrm{of}\ \mathrm{excessive}\ \mathrm{weight}\ \mathrm{regain}=\left(\frac{\mathrm{current}\ \mathrm{weight} - \mathrm{nadir}\ \mathrm{weight}}{\mathrm{excess}\ \mathrm{weight}}\right)\times 100; $$

$$ \mathrm{Percentage}\ \mathrm{of}\ \mathrm{total}\ \mathrm{weight}\ \mathrm{loss}=\left(\frac{\mathrm{weight}\ \mathrm{presurgery} - \mathrm{current}\ \mathrm{weight}}{\mathrm{weight}\ \mathrm{presurgery}}\right)\times 100; $$

$$ \mathrm{Percentage}\ \mathrm{of}\ \mathrm{excessive}\ \mathrm{weight}\ \mathrm{loss}=\left(\frac{\mathrm{weight}\ \mathrm{presurgery} - \mathrm{current}\ \mathrm{weight}}{\mathrm{excess}\ \mathrm{weight}}\right)\times 100; $$

$$ \mathrm{Percentage}\ \mathrm{of}\ \mathrm{alterable}\ \mathrm{weight}\ \mathrm{loss}=\left(\frac{\mathrm{body}\ \mathrm{mass}\ \mathrm{index}\ \mathrm{presurgery} - \mathrm{current}\ \mathrm{body}\ \mathrm{mass}\ \mathrm{index}}{\mathrm{body}\ \mathrm{mass}\ \mathrm{index}\ \mathrm{presurgery} - 13}\right)\times 100\ . $$

Excess weight will be calculated based on metropolitan guidelines [41].

Secondary outcome measures will include behavioral and psychological outcome measures: the number of days engaging in maladaptive eating behaviors (such as grazing, binge eating, or overeating episodes) as well as the number of hours of sedentary and physical activities in the previous month. Psychological symptoms assessed with self-report measures will also be tested. Differences between the intervention group and the control group will be tested at all assessment times. Additionally, midterm secondary outcomes will be tested as predictors of weight outcomes in later assessments.

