Baseline (*T*_b_), midterm (*T*_m4_ and *T*_m8_), end of treatment (*T*_f_), and follow-up (*T*_fu6_ and *T*_fu12_) data on primary and secondary outcomes will be compared between the two groups. Repeated measures gathered for the intervention group during the feedback messaging system will be used to study the effect of behavior and psychological outcomes on weight. Repeated assessment enables testing of the course of relevant factors and their relation to weight.

Moderators and nonspecific predictor variables that can affect outcomes without stemming from the intervention are assessed at baseline (*T*_b_); these variables include pre-surgery body mass index, type of surgery, sex, severity of general psychopathology, and frequency of maladaptive behaviors.

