### Statistics

Pearson’s chi-square tests will be used to analyze significant differences in the proportion of cases with weight regain and in specific outcome variables between the intervention group and the control group. Significant weight regain will be considered when higher than 5 kg. The Kaplan–Meier approach (together with the log-rank test) will be used to answer the main question of efficacy. Repeated-measures analysis of variance (ANOVA) will be conducted to explore differences between the participant groups for different key variables at various time points. The main effect for surgery type will be investigated. Variables such as log-in frequency, task submission, satisfaction with the program, socio-demographics, pre-intervention scores on self-report measures, and time since surgery will be tested as covariates and predictors of outcomes using Cox regression models. Relevant baseline differences will be included as covariates. Hierarchical linear models will be used to investigate different trajectories of relevant variables assessed from *T*_b_ to *T*_fu12._ Hierarchical linear models are the models that best fit unbalanced designs with unequal number of observations (missing data) per subject. Self-report measures (for depression, impulsiveness, eating disorder and eating patterns, body image, and general distress) will be examined by conducting an analysis of covariance to explore interference with weight outcomes. Post-hoc comparisons will be conducted using Tukey’s procedure. Controlled effect sizes will be calculated using the Cohen’s *d* statistic.

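### Midterm behaviours and symptoms are tested against later weight outcomes that already include regain from before the midterm visit, so a consequence of past regain can be reported as something that precedes it

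*Protocol article*

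**What the plan says.** Under *Primary and secondary outcome measures* the article gives five weight formulas. The two regain measures count from nadir weight to current weight. The three weight-loss measures count from pre-surgery weight or body mass index to the current value. None starts at the 4-month (T_m4) or 8-month (T_m8) visit. The same section adds that "midterm secondary outcomes will be tested as predictors of weight outcomes in later assessments".

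On the anchor, *Anthropometric measures* says of the weight history: "pre-surgery weight, and lowest weight since surgery) will be self-reported". Table 3 schedules that history at registration only. *Subjects* excludes people with regain of more than 15 % of total weight loss "since the nadir weight at the time of registration will be excluded", so smaller regain may already be present at entry.

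*Statistics* adds a kilogram criterion without a reference weight: "Significant weight regain will be considered when higher than 5 kg". Its general covariate rule is: "Relevant baseline differences will be included as covariates". The variables listed for the Cox models and the analysis-of-covariance sentence do not mention weight at a midterm visit.

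On interpretation, the third objective states: "We expect to identify fluctuations in key behaviors that precede weight regain". The *Discussion* adds that acting on such variables in advance could be key to preventing regain.

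**The concern.** A predictor measured at month 4 or 8 can precede only weight change that happens afterwards. The outcome it is tested against also contains change that happened before. A participant who regained early, and became distressed or began grazing because of it, has both a high midterm score and a high later cumulative regain, even if the score has no bearing on what follows.

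Reverse direction is plausible for these instruments. They include a measure of how weight influences areas of life, weight and shape concerns, and depression, anxiety and stress, all of which may respond to regain that has already occurred.

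At stake is the objective on what precedes regain. A test that cannot separate precursor from consequence can point the next intervention at the wrong targets.

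**Working it through.** **1. Overlap, from the article's own formulas.** For a nadir that predates the midterm visit:

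later weight − nadir = (midterm weight − nadir) + (later weight − midterm weight)

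The denominators (pre-surgery weight minus nadir, or excess weight) do not depend on the later visit. Only the second bracket follows the predictor. The weight-loss measures split in the same way with pre-surgery weight as the anchor. If nadir were updated and reached only after midterm, the regain measures would not overlap for that participant, but the weight-loss measures still would. This step needs no assumed value.

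**2. Inputs for the size.**
- From *Proposed sample size and power calculations*: 180 recruited and 20 % dropout, so 180 × 0.8 = 144 completers; alpha 0.05, taken as two-sided.
- Assumed, not in the article: ρ, the correlation of the midterm score with regain at that visit (0 to 0.3); a, the correlation of midterm regain with later regain (0.7 to 0.9); no path from the score to later regain; an unadjusted correlation test. The article does not name a model for this analysis.

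The article gives no figure for this analysis, so there is none to reproduce.

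**3. Unadjusted test.** With no forward effect, the correlation of the score with later regain is ρ × a. By Fisher's z, the rejection rate is

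Φ(z − 1.96) + Φ(−z − 1.96), with z = atanh(ρa) × √(144 − 3)

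Example: ρ = 0.2 and a = 0.7 give ρa = 0.14 and z = 0.1409 × 11.87 = 1.67, so the rejection rate is 38.7 %.

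| ρ | a = 0.7 | a = 0.8 | a = 0.9 |
|---|---|---|---|
| 0 | 5.0 % | 5.0 % | 5.0 % |
| 0.1 | 13.2 % | 15.9 % | 18.8 % |
| 0.2 | 38.7 % | 48.3 % | 58.0 % |
| 0.3 | 71.6 % | 82.8 % | 90.8 % |

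Simulation of the same model (6,000 replicates per setting) gave 13/16/19 %, 39/48/57 % and 71/83/91 % for ρ = 0.1, 0.2 and 0.3. A weaker link lowers the rate: at a = 0.4 it is 7.6 %, 15.9 % and 29.9 %.

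**4. With midterm regain in the model.** The same simulation rejected in 4.3–5.2 % of trials throughout.

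**5. Change score alone.** If past and later regain have equal variance and correlation a, the change from midterm correlates with the score at −ρ√((1 − a)/2), through regression to the mean. For ρ = 0.2 to 0.3 and a = 0.7 to 0.9 this gives rejection in about 8 % (ρ = 0.2, a = 0.9) to 28 % (ρ = 0.3, a = 0.7). If later gain is instead independent of past gain, a change score holds its level: 4,000 simulated trials per setting gave about 4.4–5.7 % with a change score and with adjustment alike. Which case applies is unknown. Adjusting for weight at the predictor visit covers both.

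**The case against.** The strongest reply is that the article names no model for this sentence. The unadjusted correlation test is this review's illustration, and covariates for a secondary predictor analysis are commonly left to a fuller document that is not shown. That stands as far as the error rates go: they belong to one possible analysis. It does not remove the overlap, because the article itself fixes the cumulative outcomes, the midterm predictors and the interest in what precedes regain.

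A second reply is that the sentence speaks of predictors, while the language of precursors attaches to the repeated data and the study of fluctuations. This is partly right. As a prognostic statement, an association between a midterm score and later cumulative regain is true even without a forward effect. It misleads only if read as what comes first.

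A third reply is that conditioning on midterm weight has a price. A behaviour that began early and had already driven regain by midterm is a genuine precursor, and adjustment does not credit that part. This stands and limits what the adjusted analysis can show.

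A reader might go further and infer that a consequence will certainly be reported as a cause. The article does not support this: inflation needs an association between midterm scores and existing regain, which it neither asserts nor quantifies. A reader might also extend the point to the weekly data, which "will be used to study the effect of behavior and psychological outcomes on weight". No lag, anchor or model is stated there, so no error is shown. The planned hierarchical models could respect time order, but nothing ties them to the midterm-predictor test.

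**Conclusion.** The concern holds in conditional form. The later outcome includes earlier regain by construction, and no stated covariate removes it. If midterm scores are related to regain already present, the test can present a consequence as a precursor.

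The size rests on correlations that are assumptions: at n = 144 and a midterm-to-later correlation of 0.7 to 0.9, about 13–19 %, 39–58 % and 71–91 % false positives for score-to-regain correlations of 0.1, 0.2 and 0.3. The rate is nominal at zero, and lower where later regain depends less on midterm regain. With midterm weight in the model it is about 5 %.

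This is a secondary, observational analysis, and the randomised comparison of the two arms is untouched. The change is worth making because it is cheap.

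**What to change.** In *Primary and secondary outcome measures*, for the midterm-predictor analysis:

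- Model later weight, or weight change from the predictor visit, with team-measured weight or regain at that visit and arm as covariates. A change score alone is not enough.
- For time-to-event models, start the clock at the midterm visit among participants who have not yet had the event.
- Base any claim that a midterm variable precedes later regain on this analysis. Report the unadjusted association as prognostic only.

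**Cost.** This is a wording change made before analysis. The team already measures weight in both arms at T_m4, T_m8 and every later assessment, so no new data or visits are needed. Intervals will be somewhat wider, and effects of a behaviour already expressed in weight by the midterm visit will not be credited. The report should say so.

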### Statistics

Pearson’s chi-square tests will be used to analyze significant differences in the proportion of cases with weight regain and in specific outcome variables between the intervention group and the control group. Significant weight regain will be considered when higher than 5 kg. The Kaplan–Meier approach (together with the log-rank test) will be used to answer the main question of efficacy. Repeated-measures analysis of variance (ANOVA) will be conducted to explore differences between the participant groups for different key variables at various time points. The main effect for surgery type will be investigated. Variables such as log-in frequency, task submission, satisfaction with the program, socio-demographics, pre-intervention scores on self-report measures, and time since surgery will be tested as covariates and predictors of outcomes using Cox regression models. Relevant baseline differences will be included as covariates. Hierarchical linear models will be used to investigate different trajectories of relevant variables assessed from *T*_b_ to *T*_fu12._ Hierarchical linear models are the models that best fit unbalanced designs with unequal number of observations (missing data) per subject. Self-report measures (for depression, impulsiveness, eating disorder and eating patterns, body image, and general distress) will be examined by conducting an analysis of covariance to explore interference with weight outcomes. Post-hoc comparisons will be conducted using Tukey’s procedure. Controlled effect sizes will be calculated using the Cohen’s *d* statistic.

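### The 5 kg regain event has no stated reference weight; if it is counted from nadir, some eligible participants who lost more than 33.3 kg can be randomised already past it

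*Protocol article*

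**What the plan says.** Three parts of the protocol article bear on this point.

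- **Entry (Subjects).** Anyone whose regain is above a limit of 15 % "of the total weight loss) since the nadir weight at the time of registration will be excluded". Regain since nadir of up to 15 % of the weight lost is therefore eligible. There is a minimum initial loss ("Significant weight loss will be considered when the percentage of excessive weight loss is higher than 30") but no upper limit on kilograms lost.
- **Outcome (Primary and secondary outcome measures).** "The primary outcome measure will be weight regain assessed at baseline", at the end of treatment and at both follow-ups. Both regain formulas, for total and for excessive regain, have current weight minus nadir weight as numerator.
- **Analysis (Statistics).** A chi-square test compares the proportions with weight regain. Then comes "Significant weight regain will be considered when higher than", with the threshold set at 5 kg. The next sentence says that the Kaplan–Meier approach ("together with the log-rank test) will be used to answer the main question of efficacy").

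The Statistics section does not give the reference weight for the 5 kg, and the Kaplan–Meier sentence does not name its event. Regain above 5 kg is the only event threshold in that section, so it is the natural reading for both the chi-square proportion and the time-to-event analysis.

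**The concern.** The entry limit is a percentage of the weight lost and the event threshold is a fixed number of kilograms. If both are counted from nadir, they do not fit together. For someone who lost a lot of weight, 15 % of the loss is more than 5 kg, so that person can meet the entry rule and the event definition on the same day.

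A time-to-event analysis of prevention needs everyone to be event-free at time zero. An event already present at randomisation cannot be prevented by the program, is expected equally often in both arms, and pulls the log-rank and chi-square comparisons towards no effect. If the reference weight is left open instead, the definition of the main efficacy event could be settled after data have been seen.

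**Working it through.** **Where the two limits cross**

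Inputs: 15 % of total weight loss (Subjects) and more than 5 kg (Statistics). Let L be pre-surgery weight minus nadir weight. The largest eligible regain since nadir is 0.15 × L. It equals 5 kg at L = 5/0.15 = 33.3 kg.

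| Weight lost to nadir (kg) | Largest eligible regain at entry (kg) | Can exceed 5 kg at entry? |
|---|---|---|
| 20 | 0.15 × 20 = 3.0 | no |
| 30 | 0.15 × 30 = 4.5 | no |
| 40 | 0.15 × 40 = 6.0 | yes |
| 50 | 0.15 × 50 = 7.5 | yes |
| 60 | 0.15 × 60 = 9.0 | yes |

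For assumed pre-surgery weights of 100, 120 and 140 kg, a loss of 33.3 kg is 33.3 %, 27.8 % and 23.8 % of body weight.

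Above 33.3 kg the overlap is possible, not certain: regain at registration must exceed 5 kg and still be no more than 15 % of the loss.

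If the 5 kg is counted from the baseline weight, everyone starts at 0 kg and nobody can be past the event.

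**Which reference the text favours**

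For nadir:
- Both regain formulas use it.
- The entry rule measures significant regain from it.
- Regain is to be assessed at baseline, where a from-baseline measure would be zero for everyone.

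For a reference in trial time:
- The safety alert (Safety aspects and ethical considerations) counts 10 kg from the start of the intervention.
- The case alarm (The weekly feedback monitoring system) counts 5 kg over the preceding 3 months.

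**How many participants, on assumptions**

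The article gives no distribution of weight loss or of regain at entry. With loss normal, mean 40 kg and SD 12, P(L > 33.3) = 1 − Φ((33.3 − 40)/12) = 71 %. The share already more than 5 kg above nadir at entry was simulated for three assumed distributions of the regain fraction. The exponential ones are cut off at 15 %, which lowers their means to about 4.2 % and 2.9 %.

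| Assumed loss (mean, SD) | Uniform 0–15 % | Exponential, mean 5 % | Exponential, mean 3 % |
|---|---|---|---|
| 30 kg, 10 | 6 % | 1 % | 0.4 % |
| 40 kg, 12 | 18 % | 5 % | 2 % |
| 45 kg, 12 | 24 % | 7 % | 2 % |

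**What it does to power, on assumptions**

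The setting is 72 per arm (90 less 20 % dropout), 37 % of controls with a true event by month 24, visits at 4, 8, 12, 18 and 24 months, and prevalent cases counted as events at the first visit in both arms. Simulated log-rank power:

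| Prevalent at entry | Hazard ratio 0.5 | Hazard ratio 0.4 |
|---|---|---|
| 0 % | 60 % | 78 % |
| 2 % | 56 % | 75 % |
| 5 % | 50 % | 69 % |

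The hazard ratios are assumptions. The 37 % is borrowed from the Background, where it refers to regain of more than 25 % of the weight lost, not to regain above 5 kg.

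**The case against.** The strongest reply is that the article never says the 5 kg is counted from nadir. The nadir formulas are percentages, while the two other kilogram thresholds for regain are anchored in trial time, one of them at the same 5 kg. Counted from baseline, the problem disappears. Nor does the article say outright that the Kaplan–Meier event is regain above 5 kg. It is also a condensed report, and the exact event definition could sit in an analysis plan that is not shown.

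The first part stands: the point is conditional. A reader might infer that participants will certainly be randomised with the event, and the text does not support that. The appeal to an unseen plan is weaker. The article itself fixes the entry limit, the formulas, the threshold and the main test, and on the only definition of regain it gives, those rules clash.

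A reader might also infer that the main test therefore fails to measure prevention at all. That is too strong: at a mean loss of 40 kg, 82 % to 98 % of participants enter event-free. Leaving out the prevalent cases would not in itself bias the comparison either, because regain is assessed at registration, before randomisation. Restricting on that value keeps the arms comparable. It narrows the population and costs little power (about 57 % against 59 % when 5 % are left out, at hazard ratio 0.5).

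Larger power losses can be produced, for example 38 % power at 15 % prevalence. They need regain at entry to be spread almost evenly up to the limit, and they count every prevalent case as an event at month 4, the most damaging handling. Nothing in the article supports that as the central case.

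**Conclusion.** The point holds in conditional form. The Statistics section does not fix the reference weight for its 5 kg event. If it is nadir, which the article's formulas and entry rule favour, eligible participants who lost more than 33.3 kg can be past the event at randomisation. The 33.3 kg follows from the article's own figures and needs no assumption beyond the nadir reading.

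The size of the effect cannot be computed from the article. With a mean loss of 40 kg (SD 12), about 2 % to 18 % of participants would be affected, depending on regain at entry. At 2 % to 5 %, power falls by about 4 to 10 percentage points from 60 % (hazard ratio 0.5, 37 % control events, 72 per arm). The effect could be smaller still if average loss or regain at entry is low, but its direction is towards no effect.

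This should be fixed, because it concerns the main efficacy event and the remedy is cheap. It does not show that the trial cannot answer its question. Confidence is moderate, since both the nadir reference and the identity of the Kaplan–Meier event are inferred.

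**What to change.** State in the Statistics section that the event for the Kaplan–Meier, log-rank, Cox and chi-square analyses is a weight measured by the research team more than 5 kg above the team-measured weight at T_b. Everyone is then event-free at time zero and nobody has to be left out after randomisation. Keep percentage regain from nadir as the continuous outcome, and report regain since nadir at entry as a baseline variable.

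The cost is one sentence and no new data: the Anthropometric measures section already has the team weigh both groups at T_b and every later assessment. A further gain is that the event no longer depends on the lowest weight since surgery, which is self-reported.

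There are two drawbacks. The event is no longer on the same scale as the nadir-based outcome. And because entry starts 12 months after surgery, some participants may still be losing weight after T_b; for them an event counted from T_b misses regain from a later, lower nadir. The continuous nadir-based outcome still captures that regain.

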### Intervention strategy of APOLO-Bari – the rationale

After initial and dramatic weight change, patients can consolidate and build on their new and healthy lifestyles during the postoperative period. Handling post-surgery demands implies the need for behavioral modifications to engage in a healthy lifestyle and to comply with prescribed nutrition guidelines, especially at later follow-up times. However, as the follow-up time increases, the number of consultations with the medical team invariably decreases, resulting in a gap between health services and patients, particularly patients who might not otherwise have access to specialized treatment because of a lack of available resources outside of urban centers. With less frequent medical appointments over time, problematic behaviors might be overlooked and might not be clinically addressed, resulting in eventual weight regain.

The novelty and strength of the program APOLO-Bari are based on the ability to monitor key patient features related to outcomes continuously, to support and guide patients continuously, and to provide cognitive-behavioral-based support during the follow-up period, either to improve results or prevent poor outcomes. This approach attempts to narrow the gap between clinical services and patients by providing long-distance support to a large number of patients simultaneously, without the need for face-to-face sessions.

However, the disadvantages of internet-based programs have been noted; hence, the feasibility of the widespread utilization of such programs is called into question: weak adherence through the minimal use of internet resources, high rates of attrition, less education and less initial weight loss have been associated with dropout rates. In contrast, various studies have shown a positive association between log-in frequency and weight loss [30]. To overcome some of these difficulties, APOLO-Bari includes interactive tools that are designed to enhance adherence to the program, such as a feedback messaging system that is based on the patient’s input and a privileged channel (chat sessions) to contact a professional directly with specific concerns.

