### Proposed sample size and power calculations

The sample size was computed by considering a 0.2 effect size, an alpha level of 0.05, a desired statistical power of 0.8, four predictors or measures and a 20 % dropout rate; this calculation suggested that a total of 180 participants should be recruited (90 in each group).

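### Longitudinal group comparisons are assigned to repeated-measures ANOVA, which conventionally drops anyone with a missed visit, although the plan names hierarchical models as best for missing data

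*Protocol article*

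**What the plan says.** The Statistics section of the protocol article gives three analyses three separate jobs.

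- Main efficacy question: Kaplan–Meier with the log-rank test "will be used to answer the main question of efficacy".
- Differences between the arms over time: "Repeated-measures analysis of variance (ANOVA) will be conducted to explore differences between the participant groups for different key variables at various time points".
- Course over time: "Hierarchical linear models will be used to investigate different trajectories of relevant variables assessed from" baseline to the 12-month follow-up. The next sentence gives the reason: "Hierarchical linear models are the models that best fit unbalanced designs with unequal number of observations (missing data) per subject". No group term or group-by-time term is stated for these models.

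The section on primary and secondary outcome measures shows how much the longitudinal comparison may carry. It says "Differences between the intervention group and the control group will be tested at all assessment times" and, after listing all six assessments, that "data on primary and secondary outcomes will be compared between the two groups". The same section first lists the primary outcome at four times only: baseline, end of treatment, and the two follow-ups.

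The sample-size section plans 180 participants, 90 per arm, with 20% dropout. The retention section makes the voucher depend on 70% of assessments, so some incomplete series are foreseen.

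**The concern.** The plan names a model that uses every observed visit, says that it is the best choice when visits are missing, and then gives the randomized comparison over time to a method that conventionally cannot use an incomplete series. This is a stated choice of method, so it differs from a detail that an article leaves to the analysis plan.

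Two things are at stake. First, participants with one missed visit lose all their data in these comparisons, which costs precision. Second, the participants who remain are no longer the randomized groups. If the reasons for leaving differ by arm and relate to earlier outcomes, the estimated difference shifts. The affected results are the longitudinal comparisons of key variables, which bear on the stated objectives for eating behavior, distress and self-concept.

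**Working it through.** **Inputs from the protocol article.** 180 randomized 1:1; 20% dropout; effect size 0.2, alpha 0.05, power 0.8; four measures or predictors; five post-baseline visits (4, 8 and 12 months, then 6 and 12 months of follow-up), of which three carry the primary outcome.

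**Assumed.** q, the chance that a retained participant misses any one visit; the within-person correlation ρ; the dropout mechanism. The article gives none of these, so ranges are shown.

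**Step 1. The plan's 180.** The section gives "considering a 0.2 effect size, an alpha level of 0.05, a desired statistical power of 0.8" but names neither the test, the effect-size metric nor ρ. Reading 0.2 as Cohen's f for the between-group test of a repeated-measures ANOVA with m = 4, the noncentrality is λ = f²·N·m / (1 + (m − 1)ρ).

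- ρ = 0.60: N = 140, λ = 0.04 × 140 × 4 / 2.80 = 8.0; 140 / 0.8 = 175.
- ρ = 0.65: N = 147, λ = 0.04 × 147 × 4 / 2.95 = 7.97; 147 / 0.8 = 184.

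So 180 is approached with an unstated ρ of about 0.60 to 0.65. The point below does not depend on how 180 was derived.

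**Step 2. Complete cases.** With 20% dropout, 180 × 0.8 = 144. With k post-baseline visits in the model, complete cases = 144 × (1 − q)^k.

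| q | k = 5 | share of 180 | k = 3 | share of 180 |
|---|---|---|---|---|
| 3% | 124 | 69% | 131 | 73% |
| 5% | 111 | 62% | 123 | 69% |
| 8% | 95 | 53% | 112 | 62% |

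**Step 3. Precision.** Take a group effect common to five post-baseline visits, f = 0.2 (d = 0.4 for two equal groups), dropout spread evenly over the visits, and missingness at random. Power = Φ(0.4·√(90·I/2) − 1.96), where I is the information per participant. With complete data I = 5 / (1 + 4ρ), which is 1.389 at ρ = 0.65. Complete cases at q = 0: I = 0.8 × 1.389 = 1.111, so 0.4 × √50 − 1.96 = 0.868 and power is 81%. The mixed model retains about 91% to 94% of the full information across these settings.

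| q | complete N | ρ = 0.65: complete-case / mixed | ρ = 0.50: complete-case / mixed |
|---|---|---|---|
| 0 | 144 | 80.8% / 86.6% | 87.3% / 91.7% |
| 2% | 130 | 76.7% / 86.5% | 83.7% / 91.5% |
| 5% | 111 | 70.1% / 86.3% | 77.8% / 91.3% |
| 10% | 85 | 58.3% / 85.9% | 66.3% / 90.9% |

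**Step 4. Bias.** Simulation with a true difference of 0.40 SD at the last visit and 20% dropout in each arm:

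| Dropout mechanism | complete-case | mixed model |
|---|---|---|
| random in both arms | 0.40 | 0.40 |
| depends on earlier values, same in both arms | 0.40 | 0.40 |
| depends on earlier values in control only | 0.27 | 0.40 |
| depends on earlier values in intervention only | 0.53 | 0.40 |
| depends in opposite directions by arm | 0.15 | 0.40 |

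A separate scenario in kilograms, with a true effect of zero over 1,500 simulated trials, had 22% intervention dropout driven by the last observed gain and 14% random control dropout. Complete cases gave −1.35 kg at 24 months and the likelihood-based model −0.01 kg, with standard errors of 1.02 and 0.98. That is one assumed mechanism, not a forecast. In all these runs the data were generated so that missingness depends only on observed values, the condition under which the mixed model is expected to be unbiased.

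**The case against.** The strongest reply is about reach. The ANOVA is worded as exploratory, and the main efficacy question has its own test. A reader might infer that the trial's headline result rests on complete cases. The Statistics section does not support that, and this part of the reply stands in full.

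A reader might also infer that dropout here is already shown not to be completely random, because the intervention rationale says "high rates of attrition, less education and less initial weight loss have been associated with dropout rates". That sentence describes internet programs in general. It does not say that regain during follow-up drives dropout in this trial, or in one arm only. Leaving the online program is also not the same as missing the outcome, since the research team measures weight in both arms.

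The fall from 180 to 144 is already in the sample-size allowance, so only losses below 144 are unplanned. The rates of intermittent missed visits are assumptions. A missing-data rule for the ANOVA could sit in an analysis plan that is not shown, and dropping incomplete cases is a property of the conventional method that the article does not itself state.

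Sphericity over unevenly spaced visits might be added as a further fault. It should not be: the group main effect does not need it, routine corrections exist for the other tests, and uneven spacing is not itself a violation.

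What remains is the allocation of methods. The article states the weaker tool for the group comparison and the stronger one, by its own account, for something else.

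**Conclusion.** The point holds for the longitudinal between-group comparisons of key variables, and only for those. Conventional repeated-measures ANOVA keeps at most 144 of 180 participants at the plan's own dropout rate. It keeps 124 to 95 if 3% to 8% miss each of five visits, or 131 to 112 if three visits are used; both ranges rest on the assumed q.

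The loss of precision needs no difference between arms. At ρ = 0.65 and q = 5%, power for a common effect of d = 0.4 is about 70% with complete cases and 86% with the mixed model.

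Bias is conditional. It arises if dropout depends on earlier outcomes differently by arm, can run in either direction, and was absent in simulation when the mechanism was the same in both arms. The documents do not establish which case applies, so no single bias figure, including −1.35 kg, should be read as the expected error.

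This should be changed, because the better model is already planned. It does not invalidate the named efficacy test.

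**What to change.** In the Statistics section, make the longitudinal between-group comparison the group-by-time contrast of the hierarchical linear model already planned. Specify all randomized participants as allocated, time as a categorical factor, all observed visits, and contrasts at the end of treatment and at the 6- and 12-month follow-ups. Keep repeated-measures ANOVA only as a complete-case sensitivity analysis.

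The cost is wording. No new data, visits or participants are needed, and the article reports that recruitment was not complete, so the change can be made before the final data exist.
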